## Abstract

**Background:**

Painful spinal metastases have been treated with conventional radiotherapy for decades, but one-third of the patients have insufficient pain relief after treatment and one-fifth need retreatment. Stereotactic radiotherapy is a method to increase the dose in the spinal metastases with a potentially longer lasting palliative effect without increasing the side effects of the treatment and thereby is expected to improve the quality of life significantly.

**Methods/Design:**

This study is a multicenter prospective randomized clinical trial comparing conventional radiotherapy (1 x 8Gy) with stereotactic radiotherapy (1 x 20Gy) for pain reduction and quality of life in patients with painful spinal metastases. A total of 386 patients will be randomized between the two treatment groups. Besides pain measured by the Dutch Brief Pain Inventory, quality of life and cost-effectiveness also will be measured. The primary outcome is pain reduction at 6 weeks after treatment. Secondary outcomes will be the time to pain response, duration of pain relief, health-related quality of life and toxicity, as well as cost-effectiveness.

**Discussion:**

This study investigates whether stereotactic radiotherapy with dose escalation for symptomatic spinal metastases can lead to improved pain reduction as compared to conventional radiotherapy without an increase of treatment-related side effects. These results will contribute to the optimization and individualization of the treatment for the patient.

**Trial registration:**

ClinicalTrials.gov identifier NCT02407795 (March 31, 2015).

## Background

Many patients diagnosed with cancer have already metastasized disease or will metastasize in time. When there are no curative options, treatment will be focused on maintaining optimal quality of life. Up to 70 % of all bony metastases are located in the spinal column. Spinal vertebral metastases can give serious pain complaints, which are likely to progress in time and thereby decrease the quality of life [1]. Besides pain or risk of fracture, these metastases may also lead to spinal cord compression. Of all patients with spinal metastases, 8 to 20 % will develop symptomatic spinal cord compression, which, untreated, will lead to neurological complications such as the inability to walk or stand.

Conventional radiotherapy has been used for decades for palliation of pain caused by bone metastases. Patients are treated in a single or multiple fractions. Generally, a reduction in pain will occur in two-thirds of patients within 4 to 6 weeks after irradiation. Retreatment is necessary in up to 24 % of all patients [2]. Various studies, randomized or retrospective, have focused on dose and fractionation schemes in an effort to increase the efficacy of radiotherapy. The majority of these studies found no evidence that a single dose of 8Gy was inferior in pain relief compared to fractionated schedules for a higher irradiation dose, although the incidence of re-irradiation was higher using a single dose [2–7]. Because of these studies, in the Netherlands, a single dose of 8Gy is mainly used for painful metastatic lesions. In recent years, the results of systemic therapies improved significantly resulting in a better median survival of patients with metastatic disease. Therefore, patients nowadays that are irradiated to a single dose of 8Gy for spinal vertebral metastases are at higher risk of relapsing at the irradiated site. Re-irradiation can be offered to the patient; however, with conventional treatment, the radiation dose that can be given may be limited by the tolerance of the spinal cord.

Stereotactic body radiotherapy (SBRT) allows dose escalation to the spinal vertebra or paraspinal tumor with steep dose gradients that limit exposure to the spinal cord and other organs at risk. As the dose to the non-involved organs at risk is strongly reduced, fewer side effects will be expected compared to conventional radiotherapy. Due to the biologically higher dose that can be given to the target volume compared to conventional radiotherapy, better results are anticipated, especially when more radio-resistant tumors like renal carcinoma or melanoma are treated. Another question to be answered is whether we can identify a subgroup of patients that will benefit more from high dose stereotactic irradiation as compared to the conventionally used single fraction of 8Gy radiotherapy.

No data are available from randomized clinical trials comparing the standard 8Gy to SBRT high dose, nor are there dedicated phase I dose escalation studies. The total dose and the fractionation schemes have been mainly dependent on the physician [8–10]. The first patients treated by stereotactic radiotherapy for spinal metastases were reported in 1995. These patients were treated with multiple fractions. As time, and therefore experience, progressed, treatment techniques improved, and the number of indications for stereotactic radiotherapy increased. Currently, SBRT is a proven successful treatment modality for brain, liver, and lung tumors, as well as metastatic disease to these organs. Currently, one other active randomized trial in the United States is investigating single fraction conventional versus stereotactic radiotherapy for spinal metastases (RTOG 0631). In that trial, a single fraction of radiotherapy with conventional 8Gy is compared to stereotactic 16Gy, with primary endpoint pain relief at 3 months after treatment. Unfortunately, no time to response is measured, no consensus delineation rules have to be used, and no standardized quality of life questionnaires are used. Finally, if the trial is negative, it may be disputed whether 16Gy is sufficiently higher relative to 8Gy for obtaining a significant improvement in pain relief. Institutions already treating patients with stereotactic radiotherapy have reported doses of 20 to 24Gy as being a standard treatment, without serious toxicity [11]. However, when patients have been treated with a single fraction dose > 20Gy, an increased risk for vertebral compression fracture has been reported, especially in patients with baseline compression fractures, lytic tumors, or spinal misalignment [12, 13].

The aim of this study is to investigate whether stereotactic radiotherapy for symptomatic spinal metastases can lead to improved pain reduction as compared to conventional radiotherapy, without an increase of treatment related side effects and thereby result in a better quality of life. The primary objective is pain reduction, but we also focus on the duration of pain relief as an important secondary endpoint besides quality of life and cost-effectiveness. To answer these questions, an intensive scheme of time points for questionnaires and pain scores will be used. These results will contribute to the optimization and individualization of the treatment for the patient.

## Methods/Design

This is a multicenter, prospective randomized clinical trial to investigate pain reduction after radiotherapy. Two different radiation doses will be evaluated: 1 x 20Gy by SBRT and 1 x 8Gy conventional radiotherapy.

### Objectives/endpoints

The primary objective is to investigate whether stereotactic radiotherapy for symptomatic spinal metastases can lead to improved pain reduction as compared to conventional radiotherapy without an increase of treatment-related side effects. The primary endpoint will be pain reduction after treatment. Secondary endpoints are time to pain response, duration of pain relief, quality of life, and toxicity. In addition, cost-effectiveness will be studied.

### Recruitment and randomization

Patients must be able to undergo radiotherapy and fulfill the eligibility criteria. The diagnosis of a solid tumor must be pathologically confirmed to make the patient eligible for the study. The extent of the metastases in the spine should be visualized on an MRI, no longer than two weeks before randomization or no longer than 6 weeks before the start of treatment. To determine the clinically relevant category of stability, the Spinal Instability Neoplastic Score (SINS) will be obtained and documented prior to treatment. Earlier studies showed that the sensitivity of SINS for potentially unstable or unstable lesions was 95.7 %, with a specificity of 79.5 % [14, 15]. Written informed consent will be obtained from all participants before entering the study.

The study is designed to be carried out in multiple centers in the Netherlands. Patient randomization will only be allowed from authorized investigators, their authorized staff members, or data manager. A patient can be randomized only after verification of eligibility. In case a patient is eligible and a written informed consent is obtained, the randomization form must be faxed or digitally sent to the Data Center. Randomization will be performed using a password-protected database (OpenClinica). Patients will be stratified on primary tumor type (breast/prostate, non-small-cell lung/renal/colorectal/sarcoma/melanoma and others), Karnofsky performance status (60 to 70 versus 80 to 100) and number of spinal metastases (single lesion, 2 to 3 lesions, and disseminated osseous lesions).

### Inclusion and exclusion criteria

Inclusion criteria are as follows:Histologically proven solid tumor with radiological diagnosis of spinal metastasesPain score minimum 2 on an 11-point scale (0 = no pain to 10 = worst imaginable pain)Maximum of two consecutive or noncontiguous spinal segments involved by tumor at current level of interestGross tumor optimally > 3 mm from the spinal cord on MRIKarnofsky performance status ≥ 60WHO 0-1-2Life expectancy > 6 weeksAge ≥ 18 yearsNonpregnant, nonlactating female patients. Sexually active patients of childbearing potential must implement effective contraceptive practices during the studyWritten informed consent

Exclusion criteria are as follows:History of previous radiotherapy to the spine at the current level of interest or overlapping locationChemotherapy or targeted systemic therapy within 14 days of radiotherapySpinal instability or neurological deficit resulting from bony compression of neural structuresPathologic fracture or impending fracture needing surgical fixationPrior surgery to the spine at the current level of interest or overlapping locationGross tumor < 3 mm from the spinal cord on MRIMore than 25 % spinal canal compromisePatients with a pacemaker such that MRI cannot be performed or the treatment cannot be delivered safelyPatients not able to undergo MRIEarlier nuclear medicine treatment for example strontium 89 treatmentPregnancyAltered mental status that would prohibit the understanding and giving of informed consent

### Assessment of the endpoints

Time to response is calculated from the date of randomization. Pain is self-reported by the patient and will be measured by an adjusted version for daily use of the Dutch Brief Pain Inventory (BPI). The BPI assesses pain on a 0–10 scale, where 0 is no pain and 10 is worst imaginable pain. It also has a questionnaire that consists of questions on severity of pain, impact of pain on daily function, location of pain, pain medications, and amount of pain relief in the past 24 hours or the past week. It is a short questionnaire that requires 5 minutes to complete. The BPI has been validated in more than 25 different languages. Response to treatment is calculated taking into account changes in the administration of opioids. Quality of life will be assessed using the EORTC QLQ-C15-PAL and the EORTC QLQ-BM22 [16–18]. These are well-validated, quality-of-life instruments specific to bone metastases. The EORTC QLQ-C15-PAL is a shortened version of the EORTC-C30, which is one of the most widely used questionnaires. The QLQ-C15-PAL consists of 15 items, and is the core questionnaire for palliative care. The QLQ-C15-PAL is supplemented by the disease specific module: the EORTC QLQ-BM22. This module is developed specifically for patients with bone metastases to evaluate the benefits and side effect of a treatment. It is intended to supplement the core questionnaire QLQ-C15-PAL and has completed all phases of testing as a reliable, validated, cross-cultural applicable module. The QLQ-BM22 contains 22 items divided into four scales assessing painful sites (five items), painful characteristics (three items), functional interference (eight items), and psychosocial aspects (six items). Both the QLQ-C15-PAL and the QLQ-BM22 questionnaires are patient rated because the gold standard for assessing symptom experience is self-reporting by the patient. The questionnaires will be available on paper or electronically, according to the wish of the patient. Toxicity is assessed using the CTC-AE 4.0. To measure the quality of the health status of the patients, the EuroQol-5D will be used [19]. In both randomization arms, the patients will be asked to fill out the following:Days 0 to 14: their daily average, worst and present pain, intake of medication (dosage), and effect of medication (BPI)Days 0, 7, and 14: effect of their pain on quality of life items (general activity, mood, walking ability, normal work, relations with other people, sleeping, enjoyment of life, and overall quality of life (EORTC-QOL)Weeks 4 and 6 and months 2, 3, 4, 6, 9, 12, and thereafter, every 6 months with a maximum of 5 years or until death, both the BPI and QOL questionnaires. Concomitant use of analgesics should be noted.

Post-treatment diagnostics should be performed according to the institutions routine guidelines. Recurrence of disease should preferably be confirmed using MRI. Tumor growth less than 25 % is classified as stable disease. Data needed for re-irradiation and the occurrence of spinal cord compression and/or fractures, along with data on systemic treatment are collected at 3-month intervals at the institutes.

The pain score will be divided into four response categories for analyses. Complete response (CR) is defined as a pain score of 0 at the treated site, with no concomitant increase in analgesic intake. Partial response (PR) is defined as a pain reduction of 2 or more at the treated side on a scale of 0 to 10 without analgesic increase, or an analgesic reduction of 25 % or more from baseline without an increase in pain. Pain progression (PP) is defined as an increase in pain score of 2 or more above baseline at the treated site with stable analgesic intake or an increase of 25 % or more in analgesic intake compared with baseline with the pain score stable or 1 point above baseline. Stable pain (SP) is defined as any response that is not captured by the complete response, partial response, or pain progression definitions. Responders are defined as CR + PR; nonresponders are defined as PP + SP.

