### Statistical analyses

The primary outcome of interest in this study is a reduction of pain of 2 points at 6 weeks since baseline. The literature shows that in patients with conventional radiotherapy the percentage of patients with pain reduction ranges from 66 % to 72 %. We assume that the percentage of patients with pain reduction is 70 % in the group with conventional radiotherapy compared to 85 % in the group with stereotactic radiotherapy. Therefore, 135 patients are needed in each group to obtain a power of 80 % (Fisher-exact test, two-sided, alpha = 0.05). We adjust for a drop-out rate of 30 % and will include a total of 386 patients. The primary analysis will be the comparison between the two treatment arms of the proportion of patients with pain reduction, defined as a decrease in pain score of at least 2 points from initial pain score, at 6 weeks. Time to pain progression, radiation-induced fracture and/or death will be calculated from date of randomization to the documentation. For the calculation of response, no fixed time interval from the date of randomization will be applied. Response of treatment will be calculated if at least two successive follow-up pain scores are available.

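### Pain up by 2 or more together with analgesics up by 25 % or more is classed as stable pain, although a smaller pain rise with the same analgesic rise is classed as progression

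*Protocol article*

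**What the plan says.** Under Assessment of the endpoints, each pain score is placed in one of four categories.

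- The best outcome is complete response: "Complete response (CR) is defined as a pain score of 0 at the treated site, with no concomitant increase in analgesic intake".
- Next comes partial response (PR), which has two limbs. The limb on pain asks for "a pain reduction of 2 or more at the treated side on a scale of 0 to 10 without analgesic increase". The alternative limb, on medication, asks for "an analgesic reduction of 25 % or more from baseline without an increase in pain".
- The third category is pain progression (PP), again with two limbs. The limb on pain asks for "an increase in pain score of 2 or more above baseline at the treated site with stable analgesic intake". The alternative limb, on medication, asks for "an increase of 25 % or more in analgesic intake compared with baseline with the pain score stable or 1 point above baseline".
- The fourth category takes the remainder: "Stable pain (SP) is defined as any response that is not captured by the complete response, partial response, or pain progression definitions".

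The categories are then paired: "Responders are defined as CR + PR; nonresponders are defined as PP + SP".

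Statistical analyses names a time-to-event quantity that involves progression: "Time to pain progression, radiation-induced fracture and/or death will be calculated from date of randomization to the documentation". It does not define progression again. The primary analysis in that section uses only a fall of at least 2 points at 6 weeks.

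**The concern.** Each limb of PP ties worsening on one measure to the other measure staying roughly level. Neither limb covers worsening on both. The residual clause does not leave that case undefined; it expressly assigns it to SP. The article therefore states a rule that gives the wrong label, and a programmer who follows the text will code it that way.

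Two things are at stake. Any table that separates PP from SP will count some clearly worse patients as stable. And if time to pain progression takes its events from PP, some events will be dated late or never recorded. Duration of pain relief, a listed secondary endpoint, would inherit the gap if its end were judged by PP, but the article does not say that it is.

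**Working it through.** **Inputs.** All rules come from Assessment of the endpoints. The minimum entry pain score of 2 comes from Inclusion and exclusion criteria. The article states no figure on this point to reproduce. Its sample size (135 per group, 386 in total) rests on the 6-week endpoint, which uses neither PP nor SP, so nothing here alters it.

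**Rules coded literally.** Let d be the change in pain score from baseline and a the percentage change in analgesic intake.

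- CR: score = 0 and a ≤ 0
- PR: (d ≤ −2 and a ≤ 0) or (a ≤ −25 and d ≤ 0)
- PP: (d ≥ 2 and a stable) or (a ≥ 25 and d is 0 or 1)
- SP: anything else

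The article does not say how much change still counts as stable intake, so two readings were run: no change at all (a = 0), and a change of less than 25 % either way.

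**Results, baseline score 5.**

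| Analgesic change | d = 0 | d = +1 | d = +2 to +5 |
|---|---|---|---|
| 0 % | SP | SP | PP |
| +10 %, stable means no change | SP | SP | SP |
| +10 %, stable means under 25 % | SP | SP | PP |
| +25 % | PP | PP | **SP** |
| +50 % | PP | PP | **SP** |
| +100 % | PP | PP | **SP** |

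The last three rows are the same under both readings, because a rise of 25 % or more is stable under neither. Two comparisons show that the order is wrong:

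- Along the +25 % row, going from 1 to 2 points worse turns PP into SP.
- Down the last column, a patient 4 points worse (5 to 9) is PP with analgesics unchanged and SP with analgesics up 50 %.

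**From visit label to event date.** Time to progression depends on the first visit that qualifies, so one SP label is not automatically a lost event. Three constructed patients, using visit times from the article, show the difference:

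- Month 3: d = +1, a = +25 %, so PP. Month 4: d = +4, a = +50 %, so SP. The event is already dated at month 3 and nothing is lost.
- Month 6: d = 0, a = 0, so SP. Month 9: d = +4, a = +50 %, so SP. Month 12: d = +1, a = +50 %, so PP. The event is dated at month 12 instead of month 9, a delay of 12 − 9 = 3 months.
- As the second patient up to month 9, with both measures staying raised at every later visit. No pain progression is ever recorded.

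**After the repair.** If the first limb covers stable or increased intake, the joint cells (3 analgesic levels × 4 pain levels = 12 in this grid) move from SP to PP. Under the no-change reading, the 4 cells at +10 % move as well. No overlap arises. With an entry score of at least 2, a rise of 2 gives a score of at least 2 + 2 = 4, so CR (score 0) is excluded. Both PR limbs rule out a pain increase. The two PP limbs stay disjoint (d ≥ 2 against d of 0 or 1). Every moved cell goes from one nonresponder class to the other, so CR + PR is unchanged.

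**The case against.** The strongest reply is that this is a narrow drafting gap with small consequences. Four parts of it deserve an answer.

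- *The first qualifying visit fixes the date.* A patient already recorded as PP keeps that event whatever label a later visit gets. This stands, and it limits the effect to patients whose first recorded worsening is joint. Pain and medication are recorded daily up to day 14, so worsening in steps is likely to be seen early on. Later visits are months apart (months 2, 3, 4, 6, 9 and 12, then every 6 months), and both measures can rise between two of them.
- *The affected quantity is peripheral.* Time to pain progression is not in the list of secondary endpoints, and no sentence says that its event is the PP category. The wording in Statistical analyses may also describe a composite with fracture and death, in which case such a patient would have the event dated at fracture or death. This stands in part: the link to PP is an inference. But the article has no other definition of pain progression.
- *Stable was meant as at least stable.* That is plausible, but the text does not say so, and the neighbouring definitions state the permitted direction of change explicitly. If that was the intention, the repair only writes it down.
- *No size can be given.* This stands. A reader might infer that the endpoint loses most of its progressors, on the ground that worsening patients are usually given more analgesics. Or a reader might assume that some share of patients is escalated and read that share as events lost. The article gives no prescribing or progression frequencies, and such a share would only restate its own assumption at visit level.

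**Conclusion.** The definition is wrong as written. Joint worsening is labelled stable pain, while a smaller pain rise with the same analgesic rise is labelled progression. This follows from the text under either reading of stable intake.

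The consequence is limited. The primary endpoint, responder status and sample size are unaffected. The PP/SP split is misstated. Time to pain progression misses or delays an event only when joint worsening is the first worsening recorded, and only if that quantity uses the PP category. The number of such events cannot be computed from the article.

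A reader might also infer bias between the arms, because the label depends partly on prescribing. The article reports nothing on prescribing by arm, so a difference can be neither shown nor excluded, and none is claimed here.

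**What to change.** Before progression is analysed, amend the first PP limb so that a pain rise of at least 2 points at the treated site counts when analgesic intake is stable or increased. Keep the second limb (analgesics up by at least 25 %, pain level or 1 point higher) and leave CR, PR and the residual class as they are.

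Nothing wider is needed. How to class a pain rise alongside an analgesic reduction is a separate choice, and the residual class need not be renamed.

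The cost is one sentence in the endpoint definition. Pain scores and medication intake are already collected. Making the change before results are known avoids the appearance that it was prompted by the data.
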